## Study Duration

The study will run for 6 years and 3 months.

## Discontinuation/Withdrawal of Participants from Study

Although we anticipate a high uptake, engagement and retention with the study due to the common first hand experience with SARS-CoV-2, participants may withdraw from the study at any stage. The information sheet clearly states the email addresses of the study investigators that can be contacted should the participant wish to withdraw from the study. No further procedures or observations will be required. Participants will have the option of leaving the study but allowing data to be kept and samples stored for research OR leaving the study, erasing all data and destroying all samples. A note will be made on the study record and the "last successful follow-up" date will be taken as the "lost to follow-up/left the study" date for the purposes of statistical analysis. Whilst the data from previous questionnaires is still able to be identified, if the study participant requests that all their data be erased or removed from the database, it will be excluded from analysis.

## Definition of End of Study

The study will end on the final follow up visit of the final recruit 6 years after the final recruit joined the study. As we aim to recruit the first ~7000 healthcare workers within the first 3 months of the study we plan to stop the study at 6 years and 3 months after starting the study. We will undertake interim analyses at the end of each year. In the unlikely scenario of all participants having undetectable antibodies we will end the study early.

# Intervention

The only interventions undertaken in this study are standardized quesionnaires (Appendix D) and blood tests (8ml) to measure the antibody titres to the SARS-CoV-2 specific protein (4ml) and 4ml EDTA to be stored for future research. These will be undertaken at each pre-planned follow up as per our flow diagrams (Appendix A). Participants will also be consented for an additional blood test of 20ml to study SARS-CoV-2 T-cell immunity and salivary sample for IgA. These optional consents will detail that samples will be tissue typed.

# Subject Withdrawal Criteria

The choice of whether to withdraw from the study is dependent on the participant. As clearly explained in the information sheet they are free to withdraw from the study at any time. For those that withdraw from the study they may choose to a) leave the study but leave all their data and samples in order to contribute to the research project or b) erase the data and destroy the samples. In the latter case clearly these participants will not be able to be considered in the final analysis. If participants choose to leave the study, but agree to the usage of their data up until the point of leaving we will consider them "lost to follow-up" at their final successful follow-up interview and serological test. We currently do not have the resources to replace subjects that withdraw from the study but should funding support be obtained we would then do so. Equally should funding allow support to recruit more patients to improve the power and reduce the detectable effect size we will do so. If full funding is obtained for the project we will aim to scale up recruit all staff members at the trust.

# Statistics

## Statistical methods to be employed (plan of analysis)

Antibody titres are expected to follow a negative exponential (log-linear) decay over time as seen following other respiratory viral infections. Serial antibody titres will be log-transformed and then multivariate linear regression models will be used to determine the predictors of antibody decay. Variable attack-rate between groups will be compared with a two-sample test of proportions and the incidence of COVID-19 disease between study groups will be compared using survival analysis with log-rank testing.

Fig.1: An estimated sample size of 4500-8000 total participants (with seropositive sample size of 1500-2700 participants, Fig.1, x-axis) provides 80% power at alpha 0.05 to detect an effect size of ≥17% decline in antibody titres over 12-months. This is based on a seropositivity prevalence of 33%, as observed in preliminary results so far and a negative exponential (log-linear) model of waning antibody titres, with 3 co-variate predictors of antibody decay, including sex, age and ethnicity (green line) or 4 co-variate predictors, including sex, age, ethnicity and co-morbidities (blue line). For comparison, the model was repeated based on 20% decline in baseline antibody titres over 12-months (using alpha 0.05), with the same 3 (orange line) or 4 (red line) co-variate predictors of antibody decline.

[figure not shown]

In order to determine the study power for varying effect sizes with unequal group sizes we undertook a two-sample power calculation of proportions with group sizes of 2100 seropositive cases and 4900 seronegative comparators using R (foundation for statistical computing) pwr function pwr.2p2n.test (Figure 2).

Figure 2. Power curve for group sizes of 2100 and 4900 participants showing that this study will have the power to detect an effect size of 0.07 i.e. a difference in the proportion in the attack rate between the two groups of 7%.

[figure not shown]

We will also undertake an exploratory analysis using survival analysis to compare the hazards of infection in both groups over the course of the study using the date of reported and PCR proven SARS-CoV-2 infection as an event and the last follow up date or the final interview as the censorship date. We anticipate a high retainment rate in the study for three reasons a) GOSH has high baseline staff retention rates b) hospital staff already understand the rationale and the importance of this research and c) we have already received high levels of interest and engagement with the study.

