- Zhang’s study of 222 patients in Wuhan during the convalescent stage (within 35 days) found 98.6% had IgG detected and 82% had IgM detected. IgG was first detected on day 4 of illness and peaked in the 4^th^ week, IgM was first detected on day 3 of illness and peaked in the 2^nd^ week.^31^
- Lou et al tested eighty patients (confirmed on PCR with deep sputum samples) using ELISA, lateral flow assays and CMIA (chemiluminescence microparticle immunoassays). ELISA performed the best of all three tests but the difference was not found to be significant. IgM and IgG seroconversion occurred at 10- and 12-days post symptom onset respectively. Antibody levels increased rapidly after day 6 post onset and by day 21 IgM seroconversion was 100% and by day 29 IgG was 97.1% (93.3% at 21days). Decline of viral load co-occurred with the rising antibody levels. At day 14 post exposure 45.5% had seroconverted. Keeping note of isolation duration times, 15.6% did not present with symptoms prior to 14 days post exposure.^15^
- To’s study of 23 patients, found at 14 days seropositivity against internal nucleoprotein (NP) was 94% for IgG and 88% for IgM. Against nucleo-capsid protein receptor binding domain (RBD), it was 100% for IgG and 94% for IgM. More patients seroconverted to IgG before IgM for both types, but this may be due to reduced sensitivity of the IgM EIA. Viral load was inversely related to antibody response. However in Zhao’s study three critical patients did not have a decline in viral load associated with increasing antibody titres.^32^ Most patients developed antibodies around day ten, one patient with severe disease developed antibodies at day 6. No genomic mutations were detected on serial sampling from four patients.^9^
- Zhao studied 173 patients and found whilst in the first 7 days following onset, PCR was more sensitive than serological tests (66.7% vs 38%), By day 12 seroconversion rates were 90% whilst PCR detection was 54% and by days 15-30 PCR detection was 45.5%. Of the patients that did not seroconvert – all samples were taken before day 13 of symptom onset.^32^ Thus, serology is especially important for patients that present late, with viral loads below the detection limit of RT-PCR.^9^

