Serological testing thus supports clinical management and will provide a key measure of the number asymptomatic cases, helping to understand the epidemiology of the virus and the true mortality rate among as a proportion of all infections. Serological testing will also assist in understanding the role of children in transmission, who comprise a low attack rate of 2.4% of cases.^6^. Furthermore, knowledge of what antibody titres are protective will enable us to track the protective duration of vaccination when this is made widely available.^33^

The sensitivity and specificity of serological testing for SARS-CoV-2 can be affected by the mode of testing. Rapid antigen lateral flow assays have the benefit of fast time to results but are likely to suffer from poor sensitivity, which has been the experience with influenza tests. Sensitivity has been as low as 60% for some lateral flow assays with the usual pre-FDA-approval test performance metrics being bypassed to expedite the availability of testing.^34^ IgM responses are often non-specific, and limit the applicability of this test for diagnosis and active management. IgG is more specific, but can take weeks to appear.^24^ In Zhao’s study median IgM was 12 days after onset and IgG was 14 days after onset.^32^

Cross reactivity with other coronaviruses must also be excluded. The abundantly expressed internal NP has 90% amino acid homology to SARS-CoV and may have potential cross-antigenicity, whereas the surface nucleo-capsid RBD is specific for SARS-CoV-2.^9^ The nucleo-capsid protein is the sole protein on the surface of the virus that is responsible for entry into human cells. It is highly conserved and abundant, thus easy to detect.^12^ This is supported by the findings of To’s study above.

In the preceding coronavirus respiratory illness epidemics, long term antibody testing demonstrated presence of neutralising antibodies for at least two years in patients following SARS, with a rapid decline in the 3^rd^ and 4^th^ years.^35,36,37^ A group of 34 health care workers were followed for SARS-CoV IgG and some had persistence up to 12 years after infection.^38^ Singapore recently reported that a patient continued to have SARS antibodies 17 years after infection.^39^ In MERS, antibodies persisted for at least 34 months in 86% (6 of 7) patients.^40^

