## Screening and Eligibility Assessment

Screening of potential applicants by study staff will occur when they attend the consent meeting (either face to face, by telephone or by zoom meeting). The process is simple and only involves ensuring that two criteria are met.

1. Either the staff member has had symptoms of possible, probable or confirmed SARS-CoV-2 infection (as defined in this protocol) and must wait for completion of 21 days from symptom onset before entering the study

OR

1. The staff member is asymptomatic but has been exposed to someone with suspected or confirmed SARS-CoV-2 infection and must wait for the completion of 21 days from the start of this exposure
2. The staff member has not had exposure to or symptoms consistent with SARS-CoV-2 infection so can enter the study immediately

Once eligibility has been confirmed, informed consent will be sought and an informed consent document completed and signed off (either face to face by the study participant or, if consent is not taken in person, then by two trained members of the study team). Study participants will then be directed to an online survey (health questionnaire) which they will need to complete to prior to arranging an appointment with the phlebotomy team for blood sampling.

All staff at GOSH will also be asked if they would like to be made aware of other parallel COVID related studies running at GOSH and UCL. If they express interest in this then they will be directed to the relevant study websites/email addresses.

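### A decay-only log-linear model combined with entry from day 21 lets some baselines precede the IgG peak cited for week 4, so the 6-month decay rate can be biased toward no decline

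*Protocol*

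**What the plan says.** Section 12.1 gives the form of the model: "Antibody titres are expected to follow a negative exponential (log-linear) decay over time as seen following other respiratory viral infections". The analysis follows from it: "Serial antibody titres will be log-transformed and then multivariate linear regression models will be used to determine the predictors of antibody decay". No rise, plateau or peak is modelled, no time origin is named, and nothing is said about samples taken before the peak. The power text in the same section describes the effect as a decline of at least 17% over 12 months, and its comparison scenario as a 20% fall from baseline, which treats baseline as the top of the curve.

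Section 9.3 sets the earliest entry. Staff who have had symptoms "must wait for completion of 21 days from symptom onset before entering the study". Exposed staff without symptoms "must wait for the completion of 21 days from the start of this exposure", but they are outside the proven-case group of the primary objective.

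Section 5.1 reports, from a study of 222 COVID-19 patients, that "IgG was first detected on day 4 of illness and peaked in the" fourth week. It also cites an average IgG peak at 20 days in SARS patients who recovered.

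Section 6 defines the primary objective as the rate of change of titres in proven cases over the 6 months following infection. Section 9.5 has seropositive participants sampled every 1 to 2 months.

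**The concern.** The fourth week of illness is days 22 to 28. A proven case bled as soon as entry is allowed can still have a rising titre. A single straight line on the log scale, fitted through a short rise and then a fall, is flatter than the fall alone.

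The first sample is also the one at the end of the time range, so it has high leverage. Over 6 months there are only about three to six samples per person. The slope is the primary result, and the effect the study is sized for is modest (17% per year, or about 9% over 6 months, since 1 − 0.83^0.5 = 0.089). A modest deficit at the first sample can therefore matter.

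**Working it through.** **Plan's own figure.** The stated 1500 to 2700 seropositive participants for 80% power cannot be reproduced: section 12.1 gives no standard deviation of log titre, no R² or f², and no number of samples per person. Only the 17% per year is borrowed below, as the true decline.

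**Inputs from the protocol.** True decline 17% per 12 months, so the true slope is ln 0.83 = −0.1863 per year; first possible sample at day 21; 1- to 2-monthly sampling; window of 6 months (to day 183).

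**Inputs assumed.** Peak at day 28, the last day of the cited week; titre at day 21 below the peak by a fraction d; a share f of cases first sampled at day 21, all others first sampled at or after the peak. No measurement noise, since only bias is at issue.

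**Formula.** Fitted slope b = Σ(tᵢ − t̄)yᵢ / Σ(tᵢ − t̄)², with y the log titre relative to peak.

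**One early-sampled person, monthly.** Samples at days 21, 51.4, 81.8, 112.2, 142.6 and 173: t̄ = 97 and Σ(tᵢ − t̄)² = 16,172.8. The weight on the first sample is (21 − 97)/16,172.8 = −0.00470 per day, or −1.715 per year. With d = 0 the slope is −0.1802, so b(d) = −0.1802 − 1.715·ln(1 − d):
- d = 5%: −0.0922, a 9% decline
- d = 10%: about 0, no decline
- d = 20%: +0.2025, an apparent 22% rise

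**One early-sampled person, 2-monthly.** Samples at days 21, 81.9 and 142.8: Σ(tᵢ − t̄)² = 7,417.6, the weight on the first sample is −2.997 per year, and b(0) = −0.1756. For d = 5%, 10% and 20% the result is a 2% decline, a 15% rise and a 64% rise.

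**Whole cohort.** Average slope = (1 − f)(−0.1863) + f·b(d), converted to a decline by 1 − exp(slope). For example, monthly with d = 20% and f = 25%: 0.75 × (−0.1863) + 0.25 × 0.2025 = −0.0891, a decline of 8.5%.

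| Assumed deficit d | Monthly, f = 10% | Monthly, f = 25% | 2-monthly, f = 10% | 2-monthly, f = 25% |
|---|---|---|---|---|
| 5% | 16.2% | 15.0% | 15.6% | 13.5% |
| 10% | 15.4% | 13.0% | 14.2% | 9.9% |
| 20% | 13.7% | 8.5% | 11.2% | 1.6% |

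The true value in every cell is 17%.

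**Sensitivity.**
- Monthly samples in 30-day steps to day 201, slightly past 6 months, give 16.4% (d = 5%, f = 10%) and 10.6% (d = 20%, f = 25%).
- With a true decline of 50% per year, monthly samples and d = 10% in 25% of cases, the estimate is 47.4%, so the bias matters less when decay is fast.
- If the fit starts at or after the peak, the true slope is recovered exactly.

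**The case against.** The strongest reply is that day 21 is a minimum and not a sampling day. Consent, an online questionnaire and a booked phlebotomy appointment come after it. Section 9.1 also sends the invitation to staff who had already tested positive in the staff testing programme, many of whom may be well past onset. Only people bled in days 21 to 28 are affected, and if the peak falls on day 22 the window is one day. All of this stands. It limits the conclusion to a bias that is possible and of unknown size.

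The week-4 peak rests on one cited study, and section 5.1 also gives an average of 20 days for SARS, before the entry threshold. That is a different virus, and an average leaves some patients with later peaks, so it weakens the point without removing it.

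Time origin and the handling of early samples are often left to a statistical analysis plan, which is not at hand. That is fair for the silence. It does not cover the model form, which section 12.1 states outright and which does not fit the protocol's own entry rule and cited peak.

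Three stronger readings are tempting, and the document does not support them:
- **Seroconversion still rising after day 21** (93.3% at day 21, 97.1% at day 29 in section 5.1). These are proportions of people positive, not titres within a person. Seropositive cases must have detectable antibodies at baseline, so late converters would mostly not supply a baseline titre.
- **One rate cannot hold over 6 years**, because section 5.1 cites "presence of neutralising antibodies for at least two years in patients following SARS, with a rapid decline in the" third and fourth years. Presence means detectability, which is compatible with steady exponential decline, and section 12.1 commits to no single rate over 6 years.
- **Covariate effects are distorted** through recruitment timing. Nothing in the protocol shows that sex, age or ethnicity is tied to the time from onset to first sample.

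**Conclusion.** The point holds as a possible bias. The stated model assumes that titres only fall; the entry rule and the cited week-4 peak allow some first samples to be taken while titres still rise. Any such sample that lies below the peak pulls the fitted 6-month slope toward no decline. A reader might infer that the primary estimate is biased, as if baselines sat at day 21; the protocol permits that but does not say it happens.

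With a true 17% annual decline, a day-28 peak, deficits of 5% to 20% and 10% to 25% of cases sampled early, the estimate lies between about 16% and 9% with monthly samples and between about 16% and 2% with 2-monthly samples. The deficit and the share are assumptions. At the low end the effect is negligible; at the high end, half or more of the decline is lost.

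**What to change.** In section 12.1, for proven cases:
- use days since symptom onset as the time axis;
- estimate the decay slope from samples taken on or after day 28, or fit a two-piece model with a changepoint at the peak;
- use earlier samples only to describe the rise and peak;
- report the fit to all samples as a sensitivity analysis, with the number of baselines taken in days 21 to 28.

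No visit or sample is added. The cost is precision. For one person, dropping the day-21 sample reduces Σ(tᵢ − t̄)² from 16,172.8 to 9,241.6 with monthly sampling, so the standard error of that slope grows by √(16,172.8/9,241.6) = 1.32. With 2-monthly sampling it falls from 7,417.6 to 1,854.4, a factor of 2. Across the cohort, with equal independent residual error and the same schedule for all, the standard error of a common slope rises by about 2% (f = 10%) or 6% (f = 25%) with monthly sampling, and by about 4% or 11% with 2-monthly sampling. If few baselines fall in days 21 to 28, almost nothing is lost.

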# Objective and purpose

| **Objectives** | **Outcome Measures/Endpoints** |
| --- | --- |
| **Primary Objective** | To determine the kinetics (rate of change) of SARS-CoV-2 specific protein antibody titres in proven cases of SARS-CoV-2 over the 6 month period following infection. |
| **Secondary Objectives** | 1. To determine the proportion of completely asymptomatic healthcare workers who have evidence of SARS-CoV-2 antibodies in their serum indicative of past infection 2. To determine the attack rate of SARS-CoV-2 in healthcare workers who have antibodies versus those who do not have antibodies 3. To determine the immune correlates of protection (antibody titres sufficient for protection) against future exposure to SARS-CoV-2 4. To investigate the roles of T-cell function and IgA in those with seropositivity to SARS-CoV-2. 5. To examine key risk factors influencing susceptibility to SARS-CoV-2. These include social determinants of health, such as housing, work and transport in the urban setting. 6. To ascertain clinical manifestations of COVID-19 disease and long term consequences of disease. 7. To pool international data in standardized form across hospital sites for longitudinal comparative review of risk factors and health service impact. 8. To assess the impact of COVID-19 on health worker staffing in hospitals and inform strategies for future planning. 9. To review antibody responses to vaccination against SARS-CoV-2 following it’s availability and analyse subsequent infection rates. |

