Within this initial planned cohort (**Study Flow Diagram 1, page 18**), a subset of ~400 staff members with confirmed symptomatic, PCR positive, antibody positive or equivocal, SARS-CoV-2 disease (and an additional 2100 staff sero-positive or equivocal staff members who were either PCR negative or asymptomatic) will be followed with intensive 1 to 2 monthly blood sampling to determine antibody titres to the SARS-CoV-2 specific protein using the *EDI^TM^* ELISA assay. Participants who are seropositive or equivocal will also have the option of providing an additional one off 20ml sample for T-cell assay analysis and a salivary sample for IgA analysis.

All 7000 recruited healthcare workers (2100 SARS-CoV-2 sero-positives and N~4900 seronegatives) will have blood taken for serological testing at baseline then at 6-monthly intervals for a total of 6 years. In addition to repeated serological testing, participants will continue as all healthcare workers at GOSH to have access to the staff testing program. This program tests symptomatic staff members by nasal swab PCR testing for SARS-CoV-2. Staff who have been tested for SARS-CoV-2 through the staff testing program will be consented for the PCR and serology results to be used in the study. All participants will also be asked to complete a detailed health and demographic questionnaire prior to each appointment, electronically. The technology design of the questionnaire will optimise participation. If key questions are missed, participants will be contacted by phone, text or email to optimise data collection and statistical analysis. As key factors impacting COVID-19 evolve, questions on review questionnaires will address these.

The data will enable us to determine the attack rate (percentage of healthcare workers with PCR proven infections/re-infections) and incidence (the rate of occurrence of disease) of SARS-CoV-2 infection amongst healthcare workers with and without antibodies. The comparison of the attack rate will indicate the protection antibodies provide. Further, the stratification of results by antibody titres, will provide information on whether a specific level of antibody confers protection.

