## Subsequent Visits

Subsequent follow-up visits will be explained to all potential study participants as part of the informed consent process. The 2100 seropositive serology cohort will be followed intensively every 1 to 2 months for repeated serological testing whilst the 4900 seronegative comparison group will be followed 6 monthly. Participants from the positive arm of the study (as well as negative controls) will have the option of providing a 20ml in EDTA sample for T-cell assay studies and tissue typing, and a salivary sample for IgA analysis, both for research purposes. As these extra assays are research tests, results will not be provided to particpants. They will be formally consented for this.

After the initial intensive phase, all ~7000 recruits will be followed 6 monthly for the 6 year duration of the study. Follow-up visits will be arranged following the baseline assessment. The same blood tests 4ml EDTA and 4ml serum will be taken at each follow up appointment as well as the same symptom questionnaire. If a COVID-19 vaccination becomes available during the study we will undertake performance evaluation of an ELISA suitable for monitoring antibody titres to the vaccine target. We will then continue to follow up our cohort with the additional focus on the antibody titres to vaccination, duration of immunity following vaccination and the attack rate in the vaccinated and unvaccinated groups (with the previso that we expect the vaccine will have wide and rapid uptake).

Further detailed questionnaires will be sent to subgroups found to have higher incidence of infection, to further delineate the susceptibility and exposure factors.

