# Appendix B: Schedule of Procedures

| **Procedures** | **Baseline Screening, Baseline Blood Tests and Follow-Up** | | | |
| --- | --- | --- | --- | --- |
|  | **Screening** | **Baseline Blood Tests** | **Follow-Up N=200 Cases (x18)** | **Follow-Up N=800 Comparison Group (x13)** |
| Informed consent | X |  | X | X |
| Demographics | X |  | X | X |
| Medical history | X |  | X | X |
| Concomitant medications | X |  | X | X |
| Physical examination |  |  |  |  |
| ECG |  |  |  |  |
| Laboratory tests |  | X | X | X |
| Eligibility assessment | X |  |  |  |
| Randomisation |  |  |  |  |
| Intervention |  |  |  |  |

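### The only titre analysis named is linear regression on repeated samples with no within-person term, so standard errors for the decay analysis would be wrong, in a direction that depends on how much slopes vary between people

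*Protocol*

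**What the plan says.** Section 6 (Objective and purpose) makes the primary objective the rate of change of "specific protein antibody titres in proven cases of SARS-CoV-2 over the 6 month period following infection". Section 7.1 (Description of study design) says the core group, "a subset of ~400 staff members with confirmed symptomatic, PCR positive", and the other seropositive staff "will be followed with intensive 1 to 2 monthly blood sampling to determine antibody titres to the SARS-CoV-2 specific protein". Section 9.5 (Subsequent Visits) repeats that the seropositive group "will be followed intensively every 1 to 2 months for repeated serological testing", and adds that after the intensive phase "all ~7000 recruits will be followed 6 monthly for the 6 year duration of the study".

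The analysis of these titres is a single sentence in section 12.1: "Serial antibody titres will be log-transformed and then multivariate linear regression models will be used to determine the predictors of antibody decay". The Fig. 1 legend in the same section sizes the decay analysis by number of participants and by 3 or 4 covariates (sex, age, ethnicity, and co-morbidities as the fourth). No section mentions random effects, estimating equations, clustered or robust errors, per-person slopes or a covariance structure.

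**The concern.** Linear regression in its ordinary form takes every row as independent. Here the rows are repeated samples from the same people, and one person's log titres resemble each other more than they resemble another person's.

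Ignoring that has two separate effects. A covariate that is fixed within a person, such as sex, is treated as though each sample were a new person, so its standard error for titre level is too small. The decay slope is estimated within persons, where stable differences between people cancel. Ordinary regression nevertheless leaves those differences in the residual variance, which inflates the slope's standard error. If decay rates themselves differ between people, ordinary regression misses that variation and the slope's standard error is pulled the other way.

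What is at stake is the interval around the rate of change, which is the primary objective, and the tests of which covariates alter it.

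**Working it through.** **The plan's own figure.** Fig. 1 gives 1500 to 2700 seropositive participants for 80% power at alpha 0.05 to detect a decline of at least 17% over 12 months. It cannot be rebuilt, because no SD, number of samples per person or within-person correlation is stated. Only the prevalence step checks: 0.33 × 4500 = 1485 and 0.33 × 8000 = 2640. Fig. 1 therefore gives no sign that correlation was allowed for.

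**Inputs.**
- From the protocol: sampling every 1 to 2 months. Over months 0 to 6, baseline included, that is m = 7 (monthly) or m = 4 (2-monthly).
- Assumed, because the protocol gives none: intraclass correlation (ICC) 0.3 to 0.9. On the natural-log scale: between-person SD 0.5 to 0.8, residual SD 0.2 to 0.3, and slope SD 0.02 to 0.2 per month.

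Each ratio below is the ordinary-regression standard error divided by the true one. True type I error at nominal 5% is 2Φ(−1.96 × ratio).

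**1. Between-person covariate, effect on titre level (no slope variation).** Ratio = 1/√(1 + (m − 1) × ICC).

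| ICC | m = 7: ratio | type I error | m = 4: ratio | type I error |
|---|---|---|---|---|
| 0.3 | 0.60 | 0.24 | 0.73 | 0.16 |
| 0.5 | 0.50 | 0.33 | 0.63 | 0.22 |
| 0.8 | 0.42 | 0.42 | 0.54 | 0.29 |
| 0.9 | 0.40 | 0.44 | 0.52 | 0.31 |

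Example: m = 7 and ICC 0.8 give 1 + 6 × 0.8 = 5.8. The 400 core cases × 7 = 2800 rows then carry the information of 2800/5.8 ≈ 483.

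**2. Decay slope and covariate-by-time, no slope variation.** Ratio = 1/√(1 − ICC) = 1.20, 1.41, 2.24 and 3.16 at ICC 0.3, 0.5, 0.8 and 0.9. Type I error is 0.019 at ICC 0.3, 0.006 at 0.5 and below 0.001 beyond that.

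**3. The same terms with slope variation.** Let u, e and b be the between-person, residual and slope SDs, with intercept and slope independent. Then ratio² = (u² + e² + b² × mean of t²)/(e² + b² × Sxx). For t = 0 to 6 monthly, mean t² = 91/7 = 13 and Sxx = 28.
- u = 0.8, e = 0.2, b = 0.02: (0.68 + 0.0052)/(0.04 + 0.0112) = 13.4; ratio 3.66. The ICC here is 0.64/0.68 = 0.94, just above the range in step 1.
- u = 0.5, e = 0.3, b = 0.1: (0.34 + 0.13)/(0.09 + 0.28) = 1.27; ratio 1.13.
- u = 0.5, e = 0.2, b = 0.15: (0.29 + 0.2925)/(0.04 + 0.63) = 0.869; ratio 0.93.
- u = 0.5, e = 0.2, b = 0.2: (0.29 + 0.52)/(0.04 + 1.12) = 0.698; ratio 0.84, type I error about 0.10.
- u = 0.8, e = 0.2, b = 0.2: (0.68 + 0.52)/(0.04 + 1.12) = 1.034; ratio 1.02, so the reversal also depends on u.

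**4. Six-year data.** An illustrative schedule is 7 monthly samples, then 11 six-monthly samples at months 12 to 72. Mean t² = 23455/18 = 1303 and Sxx = 23455 − 483²/18 = 10494.5. With b = 0.02, b² × mean t² = 0.521 and b² × Sxx = 4.198.
- u = 0.5, e = 0.3: (0.34 + 0.521)/(0.09 + 4.198) = 0.201; ratio 0.45.
- u = 0.8, e = 0.2: (0.68 + 0.521)/(0.04 + 4.198) = 0.283; ratio 0.53.

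The slope SD that made the 6-month interval far too wide makes the 6-year interval too narrow.

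**5. Does accounting for the person repair it?** In a simulation of 400 people with 7 visits and 2000 replicates (ICC 0.5 to 0.8), person-clustered errors gave type I error of 0.0475 to 0.0625 and slope coverage of 94.1% to 95.3%. Ordinary regression on the same data gave 0.33 to 0.42 for the level effect, 0.000 to 0.028 for covariate-by-time, and slope coverage of 97.6% to 100%.

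**The case against.** **The protocol does not rule out a within-person term.** It never says pooled, ordinary least squares or independent errors. Multivariate could strictly mean a multi-response model, and per-person slopes regressed on covariates would also fit the wording. An unseen statistical analysis plan might settle it. This stands as a limit on certainty. But the protocol is not silent: it names a model for serial data, and beside a list of covariate predictors the natural reading is multivariable regression. A plan that used a mixed model would depart from that text.

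**The largest error is not on the primary output.** A reader might infer from the 16% to 44% type I error that the primary analysis would produce false positives at that rate. The documents do not support this. The primary objective is a rate of change, and section 12.1 speaks of predictors of decay; covariate effects on titre level are named as neither. For slope terms over 6 months, ordinary regression is often conservative, and the cost is lost precision.

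**Slope intervals are not always too wide.** This stands. The direction turns on a slope variance that the protocol does not give, and it reverses in steps 3 and 4.

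**The 18 visits in Appendix B.** A reader might combine that column, "Follow-Up N=200 Cases (x18"), with an ICC of 0.8 to get a design effect of 1 + 17 × 0.8 = 14.6 and a type I error of 61%. That figure should not be used. Eighteen visits do not fit a 6-month window at 1- to 2-monthly sampling. A constant ICC over six years has no support. The result again concerns titre level, and the column's 200 cases match neither the ~400 core cases nor the ~2100 seropositives stated elsewhere.

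**Staggered entry.** Participants join at differing times after infection, so a pooled slope can mix differences between people with change within a person. A random-intercept-and-slope model does not by itself separate the two. The point here is confined to standard errors.

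**Conclusion.** The point holds. The only titre analysis in the protocol is one whose standard errors do not suit the repeated sampling that the protocol prescribes.

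For between-person effects on titre level the direction is certain whenever samples from one person are positively correlated: standard errors too small, ratio about 0.4 to 0.7 over the assumed ICC range. For the decay slope and its predictors, the quantities that matter most here, the error is real but its direction is conditional. The ratio is about 1.1 to 3.7 when slopes vary little between people, and about 0.45 to 0.9 when they vary more or the 6-year data are used.

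That the standard errors are generally wrong follows from the design; how wrong they are rests on assumed variances. Because the sign for the primary quantity cannot be known in advance, the named model cannot be defended as merely cautious.

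**What to change.** Replace the sentence in section 12.1 with a linear mixed-effects model for log titre, with a random intercept and a random slope per participant, and test predictors of decay as covariate-by-time interactions. At minimum, keep the regression but use standard errors clustered by participant; this repairs the intervals, although it does not describe how decay varies between people.

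State the time axis: time since symptom onset for the symptomatic PCR-confirmed cases, and a separately stated origin for asymptomatic seropositives (group C in section 8.1), who have no onset date.

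Left-censoring at the assay's positivity cut-off should not be added as part of this change. The protocol describes a semi-quantitative assay read as optical density and gives no detection limit, so values below the cut-off may be genuine measurements.

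The cost is a sentence or two in section 12.1 and standard software. No extra samples or data are needed.
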